**Trial design:**

A pre-test post-test randomized control trail.

**Ethical consideration:**

This research will be approved by the Research Ethical Committee (REC)/UoS. Consent forms will be distributed to participants prior to data collection. The participants will be informed that their data will be used for the study only. Privacy and confidentiality will be maintained by using coding system for data. The data will be stored on a locked-password-required computer in the primary investigator's office and will be accessed by the study's researchers only. Participation in this study is completely voluntary. The participant has the right to leave the study at any time. This will not result in any penalty or loss of benefits to which they are entitled to. If the participant decides to withdraw, any data taken from them will not be used in the research and will be destroyed.

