### **Basic assumptions:**

1. All subjects will attend the assessment sessions
2. All the subjects will receive the intervention as established
3. The modality will be properly calibrated

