**Sample size estimation:**

A pilot study will be conducted to detect the effect size required (at alpha level of 0.05 and power of 0.8)

A priori power analysis will be performed (G\*power, version 3.1.9.3, Duesseldorf, Germany), based on previous studies on PF

Pain, considered the Primary outcome measure and revealing a visual analogue scale (VAS) of 4-10 on the pain scale for PF.

Function limitation considered the secondary outcome measure and exposing a Foot Function Index of 100/170 or at least 60%.

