### **Randomization & Allocation**

In this study, patients will be randomly divided into two groups of equal number.

Restricted randomized sampling will be used in this study for randomization of the participants into three groups. Using permuted block randomization, with 1:1:1 allocation ratio. In a three group design, Blocks having equal numbers of As, Bs and Cs (A = intervention 1 and B = intervention 2, and C= control) are used, with the order of treatments within the block being randomly permuted

The groups will be:

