#### Control group - C:

This group will receive the same physiotherapy program in addition to sham shock wave therapy

The pain and function improvement will be assessed before and after 6 sessions. An additional assessment will be performed at the end of the 12th week for a short follow-up

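### Destroying the data of participants who withdraw rules out an analysis of everyone as randomised and can bias the comparison between arms

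*Protocol*

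**What the plan says.** The Trial design section describes the study as "A pre-test post-test randomized control trail". The Randomization & Allocation section sets out the allocation: "Using permuted block randomization, with 1:1:1 allocation ratio". Groups A and B receive shock wave therapy at different frequency and pressure settings, and group C receives sham.

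On leaving the study, the Ethical consideration section says "The participant has the right to leave the study at any time". For a participant who decides to withdraw, "any data taken from them will not be used in the research and will be destroyed". Nothing else in the protocol qualifies this. The protocol does not distinguish stopping treatment, leaving the study and withdrawing consent to the use of data.

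The Basic assumptions section takes it that "All subjects will attend the assessment sessions" and that everyone receives the intervention as set out.

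The assessment schedule is spread over two sections. Under Control group - C, "The pain and function improvement will be assessed before and after 6 sessions", with a further assessment at the end of week 12. The Data collection section adds one after three sessions. Pain on the VAS is primary and the Foot Function Index secondary. The Statistical method section compares groups with unpaired t-tests.

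**The concern.** Randomisation makes the arms comparable as allocated. Excluding people because of a later event gives up that protection, and this rule does so irreversibly. An analysis plan can choose an analysis set or a method for missing values, but it cannot bring back records that have been destroyed. The point is therefore about a rule the protocol states, not about detail it leaves for later.

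Outcome-related and unequal withdrawal is plausible here. The active arms differ in settings and one arm is sham. Participants are blinded to the parameters, but they can still notice discomfort or lack of benefit, and either could prompt withdrawal. Pain is also the primary outcome. The protocol has no other safeguard, since it assumes full attendance and its between-group test makes no adjustment for selective loss.

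**Working it through.** **1. What is lost, by time of withdrawal.**

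| Withdrawal happens | Destroyed under the rule | Final value available if data were kept? |
|---|---|---|
| After baseline, before the 3-session assessment | Baseline | No |
| After the 3-session, before the 6-session assessment | Baseline, 3-session | No |
| After the 6-session assessment, before week 12 | Baseline, 3-session, 6-session | Yes for 6 sessions, no for week 12 |

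In the third row the rule destroys a post-treatment outcome already measured. In the first two it destroys the values needed to compare withdrawers with the rest, or to model the missing outcome.

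**2. Inputs for an illustration.** The protocol has no figure to reproduce. It gives "at alpha level of 0.05 and power of 0.8", while the effect size is still to come: "A pilot study will be conducted to detect the effect size required". Assumed here: two-sided alpha; standardised effect 0.5 (0.3 and 0.8 also tried); VAS SD 2 cm (range 1.5 to 2.5); withdrawal of 5% to 30%.

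**3. Upper bound on the shift.** If the fraction p with the highest pain leaves an arm and is deleted, the mean of a standard normal outcome falls by φ(z)/(1 − p), where z is the (1 − p) quantile.

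| p | Shift in arm mean (SD) | Difference from an arm losing its worst 5% (SD) | In cm at SD 2 |
|---|---|---|---|
| 5% | 0.109 | – | – |
| 10% | 0.195 | 0.09 | 0.17 |
| 15% | 0.274 | 0.17 | 0.33 |
| 20% | 0.350 | 0.24 | 0.48 |

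If only one arm loses people, the full shift applies: 0.195, 0.350 or 0.497 SD at 10%, 20% or 30%. That is 0.39, 0.70 or 0.99 cm at SD 2, and 0.29 to 1.24 cm over the whole SD range.

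**4. Less extreme withdrawal.** Let the propensity to withdraw be u = ρy + √(1 − ρ²)e, where y is the outcome and e is independent noise. A person withdraws if u exceeds the quantile that gives the arm's rate. There is no true effect, an unpaired t-test is used, and each setting has 20,000 simulated trials.

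| n per arm | Withdrawal | ρ = 0 | 0.3 | 0.5 | 0.7 |
|---|---|---|---|---|---|
| 63 | 20% vs 20% | 5.0% | 5.0% | 5.0% | 5.2% |
| 63 | 20% vs 5% | 5.1% | 6.8% | 10.0% | 15.6% |
| 63 | 30% vs 5% | 4.9% | 8.9% | 17.1% | 31.3% |
| 25 | 20% vs 5% | 5.0% | 5.6% | 6.7% | 8.7% |

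As a cross-check, the expected shift is ρ times the upper bound. For 20% vs 5% and ρ = 0.5 that is 0.5 × 0.241 = 0.12 SD, against 0.121 simulated.

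**5. Power.** n = 2(1.96 + 0.842)²/0.5² gives 63 per arm. With m left per arm, power is Φ(0.5√(m/2) − 1.96):
- 10% lost: m = 56.7, power 76%.
- 20% lost: m = 50.4, power 71%.
- 30% lost: m = 44.1, power 65%.

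Results at effects of 0.3 and 0.8 are almost the same. Recruiting 63/0.9 = 70 or 63/0.8 ≈ 79 per arm restores power but leaves the shift in steps 3 and 4 untouched.

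**The case against.** The strongest objection is that steps 3 to 5 mostly measure missing final outcomes rather than the deletion rule. Someone who leaves before the 6-session assessment has no final VAS whether or not earlier data are kept. With the planned t-tests on available values, the shift and the power loss would be the same. This stands. The rule's own contribution is the post-treatment values of those who withdraw after the 6-session assessment, and the loss of any means to examine or model the rest.

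Three stronger readings are tempting, and the protocol does not support them:
- A reader might infer that a completers-only analysis is forced. The rule applies to those who decide to withdraw; missing sessions or a visit is not said to trigger it. The two may coincide in practice because the protocol never separates them, but that is an ambiguity rather than a stated rule. Nor do all assessments depend on completing six sessions, since one is set at week 12.
- A reader might infer that attrition by arm cannot be reported. Permuted-block allocation implies a list separate from the outcome data, and nothing says that list is destroyed. If it is kept, randomised minus analysed gives the counts. What is lost is the withdrawers' characteristics, interim values and probably their reasons.
- A reader might infer that the randomised comparison is bound to be biased. Step 4 shows little or no effect when withdrawal is unrelated to outcome, or when rates and mechanism are the same in both arms.

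It is also fair to say that the consent text is not shown and that the ethics committee may have its own view on destruction, so the change is not the investigators' alone to make.

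**Conclusion.** The concern holds in this limited form. The protocol fixes a rule that excludes randomised participants on a post-randomisation event and irreversibly destroys their data. For anyone who withdraws, it prevents analysis as randomised, sensitivity analysis based on their observed values, and description at baseline. It can bias the comparison if withdrawal is related to pain and differs between arms.

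Confidence is high on what the rule says and prevents, and low on the size of any bias. The protocol gives no sample size, SD, effect size or dropout rate, so every figure above is an illustration on assumed inputs. The shifts in step 3 are upper bounds for the withdrawal rates assumed. The type I error figures depend on the assumed correlation and on unequal withdrawal, and part of both would occur even with earlier data retained. The case for acting now rests on irreversibility: data destroyed as promised to participants cannot be recovered later.

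**What to change.** Before ethics approval, amend the withdrawal sentence in the Ethical consideration section, and the matching consent text, as follows:

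- Coded data collected up to withdrawal are kept and analysed in the arm to which the participant was randomised, unless the participant asks for erasure. This is subject to the ethics committee's agreement.
- Distinguish stopping treatment, withdrawing from the study, and withdrawing consent to the use of data. Invite those who only stop treatment to the VAS and FFI assessments already scheduled, if they are willing.
- Keep the allocation list. For each withdrawal, record the arm, the date and, where given, the reason.

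The cost is a wording change that needs ethics committee agreement, plus minor record keeping. The Ethical consideration and Recruitment sections both describe approval as still to be obtained, so on the protocol's own account the change can be made in time. Retention does not supply outcomes never measured, so assumptions about those will still have to be stated in the analysis.

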**Sample size estimation:**

A pilot study will be conducted to detect the effect size required (at alpha level of 0.05 and power of 0.8)

A priori power analysis will be performed (G\*power, version 3.1.9.3, Duesseldorf, Germany), based on previous studies on PF

Pain, considered the Primary outcome measure and revealing a visual analogue scale (VAS) of 4-10 on the pain scale for PF.

Function limitation considered the secondary outcome measure and exposing a Foot Function Index of 100/170 or at least 60%.

## **Randomization (Recruitment and allocation):**

### **Recruitment**

The patients with plantar fasciitis will be recruited from the Physical Therapy and Rehabilitation Center (out-patient) in Alain hospital, UAE. The purpose of the study will be explained to all participants before the start the assessment. A written consent forms will be signed after explanation.

Ethical approval will be obtained from education department of Alain hospital or from the University of Sharjah

### **Randomization & Allocation**

In this study, patients will be randomly divided into two groups of equal number.

Restricted randomized sampling will be used in this study for randomization of the participants into three groups. Using permuted block randomization, with 1:1:1 allocation ratio. In a three group design, Blocks having equal numbers of As, Bs and Cs (A = intervention 1 and B = intervention 2, and C= control) are used, with the order of treatments within the block being randomly permuted

The groups will be:

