#### **Data collection:**

The mean and Standard Deviation of pain scores which will be calculated before, during and after the intervention for all participants in both group.

- First assessment will be done before the intervention
- Second assessment will be done after 3 sessions
- Follow up assessment after the complete 6 sessions

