### Extracorporeal shockwave therapy (ESWT):

Extracorporeal shockwave therapy (physiotur) with Handpiece 12 mm will be set for the study group with the continues mode, frequency 15 Hz on heel, pressure of 3 and impulses of 1600. On the other hand, the parameter for controlled group will be set with frequency 10 Hz on heel, pressure of 4 and impulses of 800. Then apply it to the patients on painful area of the heel at different points (center and medial aspect of the heel) and will apply 200 impulses in each painful points till complete 1600 impulses with patients in the study group and 800 impulses with patients in the control group. The patients will be on prone position with rest both legs on the sigmoid wedge.

The program of strengthening and stretching exercises will be same for both groups combined with shockwave therapy but with different parameter in each group. Both groups will receive the intervention six times ( one time per week over two months) and will follow with home exercises program.

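### The protocol contradicts itself on the number of arms (two or three) and on whether the control group receives sham or active shock wave

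*Protocol*

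**What the plan says.** All places are in the Protocol. Unless noted, they are in Chapter III.

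- **Randomization & Allocation** opens with two groups: "In this study, patients will be randomly divided into two groups of equal number". It continues: "Restricted randomized sampling will be used in this study for randomization of the participants into three groups". Then: "Using permuted block randomization, with 1:1:1 allocation ratio". The blocks hold As, Bs and Cs, with C as control.
- **Intervention group A**: physiotherapy plus shock wave at 15 Hz, pressure 3, 1800 impulses.
- **Intervention group B**: the same physiotherapy plus shock wave at 10 Hz, pressure 4, 1800 impulses.
- **Control group - C**: "This group will receive the same physiotherapy program in addition to sham shock wave therapy".
- **Data collection** summarises pain scores "for all participants in both group". **Interventions** likewise gives the physiotherapy programme to two groups.
- **Extracorporeal shockwave therapy (ESWT)** describes a study group (15 Hz, pressure 3, 1600 impulses) and a control group: "the parameter for controlled group will be set with frequency 10 Hz on heel, pressure of 4 and impulses of 800". It repeats the counts: "till complete 1600 impulses with patients in the study group and 800 impulses with patients in the control group". It adds that the groups share the exercise programme and each receive shock wave, with different settings.
- **Statistical method** names paired and unpaired t-tests and gives no number of groups.
- In Chapter I, **Statement of the problem**, **Purpose of the study** and **Hypothesis** concern the difference between protocols. **Significance of the study** speaks of providing evidence that both protocols are effective.

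**The concern.** A randomisation list needs one number of arms, and a control patient needs one defined treatment. The protocol gives two answers to each question. Staff who work from the arm descriptions would give control patients sham. Staff who work from the ESWT section would give patients labelled control active shock wave, and the sham contrast would be lost.

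What the trial can conclude also depends on the answer. With A and B alone, both on the same exercise programme, improvement common to the two arms cannot be separated from the effect of exercise or from natural recovery. A sham arm is what would allow a statement about each protocol's own effect. In addition, if an active arm is labelled control, an active-versus-active result may be reported as active versus control.

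**Working it through.** The document gives no sample size, effect size or standard deviation, so there is no stated figure to reproduce. The main check is to set the sections side by side.

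| Section | Number of groups | Control treatment | Impulses |
|---|---|---|---|
| Randomization & Allocation, first sentence | 2, equal size | not given | not given |
| Randomization & Allocation, remainder | 3, at 1:1:1 | C = control | not given |
| Group A / B / C descriptions | 3 | sham | A 1800, B 1800 |
| Data collection | 2 | not given | not given |
| Interventions (physiotherapy) | 2 | not given | not given |
| ESWT | 2 | active, 10 Hz, pressure 4 | study 1600, control 800 |

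**Step 1, number of arms.** The allocation section conflicts with itself. The arm descriptions support three; Data collection, Interventions and ESWT support two.

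**Step 2, control condition.** Sham appears only under Control group - C. The ESWT section gives its control group active shock wave and has no procedure for delivering sham.

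**Step 3, can relabelling resolve it?** Suppose the ESWT section's study group is A and its control group is B. Frequency and pressure then match (15 Hz and 3; 10 Hz and 4). Impulses do not:

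- A: 1800 against 1600, a difference of 200.
- B: 1800 against 800, a difference of 1000.
- The ESWT section applies 200 impulses per point, so 1600/200 = 8 applications and 800/200 = 4, whereas 1800/200 = 9.

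Relabelling therefore leaves the active arms contradictory, and C still has no delivery text.

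**Step 4, consequence for sample size.** At n per arm the totals are 2n and 3n, and 3n/2n = 1.5. Three arms need 50% more patients, whatever n is. For illustration, take alpha 0.05 (two-sided, an assumption because the protocol does not state sidedness), power 0.80, and assumed standardised effects d. Then n per arm = 2 × (1.960 + 0.842)² / d² = 15.70/d², rounded up:

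| Assumed d | n per arm | Two arms | Three arms |
|---|---|---|---|
| 0.3 | 175 | 350 | 525 |
| 0.5 | 63 | 126 | 189 |
| 0.65 | 38 | 76 | 114 |
| 0.8 | 25 | 50 | 75 |

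These totals allow for neither dropout nor multiple comparisons. If all three pairs were tested at 0.05/3, the three-arm totals would be 699, 252, 150 and 99, about twice the two-arm totals.

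**The case against.** The strongest reply is that the three-arm design is plain enough. The permuted-block text with As, Bs and Cs and the three arm headings specify a usable randomisation list, and the two-group wording looks like a remnant of a two-arm plan in which the control group was today's B. The part about the list stands: the main obstacle to running the trial is the delivery text. The remnant explanation is plausible because frequency and pressure match B, but it is an inference, and the impulse counts contradict it as the document stands.

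A reader might also draw stronger conclusions that the document does not support:

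- *Without sham the trial fails its stated purpose.* It does not. The problem statement, purpose and hypothesis all concern a difference between protocols, which two arms can test. Only the sentence under Significance of the study needs a sham comparison.
- *The analysis text excludes arm C.* It does not. Statistical method states no number of groups, and unpaired t-tests can be run pairwise across three arms. Further detail may properly sit in the statistical analysis plan.
- *A specific amount of power is lost.* No total is fixed. Sample size estimation leaves it to a pilot study and a later calculation at power 0.8, so a loss computed at one assumed total and effect would describe the assumption and not the plan.
- *The three-arm sham design is the right one and the ESWT text should be struck out.* The document does not settle this, and deleting the 10 Hz text could remove the delivery description that belongs to group B.

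**Conclusion.** The contradiction is in the current text, and no other section resolves it. It covers the number of arms (two or three), the control treatment (sham or active) and, linked to these, the impulse counts (1800 and 1800 against 1600 and 800).

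It must be settled before the first randomisation, because analysis cannot restore a sham comparison once control patients have received active shock wave. Two of the three possible contrasts, A versus sham and B versus sham, exist only under the three-arm reading; A versus B exists under both.

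The 50% difference in total sample size rests only on equal numbers per arm. The absolute totals shown are illustrations on assumed effects. Which design or which settings are right cannot be told from the document.

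**What to change.** Before the first randomisation, the sponsor should:

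1. State one number of arms and one control condition.
2. Reconcile Randomization & Allocation and the three arm descriptions with Data collection, Interventions and ESWT. This includes using one set of arm labels throughout and resolving the impulse counts. If a sham arm is kept, the delivery section should cover it.
3. Let the randomisation list, the planned power analysis under Sample size estimation and the between-group contrasts under Statistical method follow that single design.
4. If two arms are confirmed, remove the statement under Significance of the study that both protocols will be shown to be effective.

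The cost is protocol wording. The number of patients is not yet fixed, so settling the design now means the power analysis is done once, for the right number of arms.

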#### Intervention group A:

The patients in this group will receive selected physical therapy program combined with shockwave therapy (ESWT) of these parameters :

1. Frequency : ( 15 Hz ) on heel
2. Intensity / pressure: 3
3. Impulses 1800
4. Number of Sessions : 6 session (1 per week)

#### Intervention group B:

The patients in this group will receive the same selected physical therapy program combined with shockwave therapy (ESWT) but with different parameters :

1. Frequency : (10 Hz ) on heel
2. Intensity / pressure: 4
3. Impulses 1800
4. Number of Sessions : 6 session (1 per week)

#### Control group - C:

This group will receive the same physiotherapy program in addition to sham shock wave therapy

The pain and function improvement will be assessed before and after 6 sessions. An additional assessment will be performed at the end of the 12th week for a short follow-up

#### **Blinding:**

In this study:

- The participants will be blinded from the parameters of the intervention used.

#### **Data collection:**

The mean and Standard Deviation of pain scores which will be calculated before, during and after the intervention for all participants in both group.

- First assessment will be done before the intervention
- Second assessment will be done after 3 sessions
- Follow up assessment after the complete 6 sessions

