### **Purpose of the study:**

The purpose of this study is to compare the results of different protocol of extracorporeal shockwave therapy on improving function with plantar fasciitis and reducing the pain after 6 sessions of the intervention.

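### The post-treatment assessment is triggered by completing six sessions, not by time from randomisation, so it is undefined for patients who stop treatment early and may drift for those who miss weeks

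*Protocol*

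**What the plan says.** All of this is in the Protocol.

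- **Data collection** lists three assessments. The first is before the intervention. The other two are defined only by sessions received: "Second assessment will be done after 3 sessions" and "Follow up assessment after the complete 6 sessions". Neither has a week, a day or a window.
- **Control group - C**, in text that applies to the whole trial, repeats the session-based definition: "The pain and function improvement will be assessed before and after 6 sessions". It then adds one visit set by the calendar: "An additional assessment will be performed at the end of the 12 th week for a short follow-up". The starting point of that count is not given, and the visit is absent from the Data collection list.
- **Purpose of the study** frames the comparison as "reducing the pain after 6 sessions of the intervention". No primary time point is formally named.
- **Basic assumptions** supposes full attendance at assessments and also full treatment: "All the subjects will receive the intervention as established".
- **Intervention groups A and B** each have six weekly sessions. The section on **Extracorporeal shockwave therapy** also says six weekly sessions but spreads them across two months.
- **Ethical consideration** has the data of anyone who withdraws destroyed. It does not distinguish stopping treatment from leaving the study.

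**The concern.** A visit triggered by the sixth session exists only for patients who reach it. A patient who stays in the study but stops after session 4, through discomfort, recovery or lack of benefit, never meets the trigger. The protocol gives no other date for that patient's post-treatment VAS (the primary outcome measure) or FFI. A patient who misses weeks and makes them up reaches the trigger later than one who attends every week.

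Completing six sessions happens after randomisation, and the arms differ in frequency and pressure or are sham, so completion can depend on the arm. If so, the unpaired comparison at this visit contrasts those who finished treatment rather than the groups as randomised. Variable timing would also mix treatment effect with time since onset of care. An analysis plan cannot recover measurements that were never taken, so this has to be settled in the protocol.

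**Working it through.** The protocol states no sample size, effect size, standard deviation or stopping rate, so there is no figure of its own to reproduce. The check has three parts.

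**1. Which assessments an early stopper has under the text as written**

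- Stops after session 2: baseline, yes; three-session, trigger not met; post-treatment, trigger not met; week 12, yes if held.
- Stops after session 4: baseline and three-session, yes; post-treatment, trigger not met; week 12, yes if held.
- Completes six sessions: all assessments.
- Completes six sessions with two missed weeks made up later (an assumption; the protocol is silent on make-up sessions): all assessments, but the last session falls 2 × 7 = 14 days later than for a patient who attends weekly.

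The gap is therefore specific. The post-treatment measurement has no definition for non-completers, and its date is free for late completers.

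**2. The planned calendar**

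Count from the first session as day 0.

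- Six weekly sessions: the last is on day (6 − 1) × 7 = 35. The end of week six is day 6 × 7 = 42.
- Two months: day 56 to 61.
- Difference from day 35: 56 − 35 = 21 to 61 − 35 = 26 days (3.0 to 3.7 weeks). From day 42: 14 to 19 days (2.0 to 2.7 weeks).
- Week 12, if counted from the first session, ends on day 84. The interval since the last session is then 84 − 35 = 49 days on the weekly reading, down to 84 − 61 = 23 days on the two-month reading.

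This spread lies between two statements of the planned calendar. It shows that the trigger cannot yet be turned into a date. It does not measure how far patients or arms would differ.

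**3. Form of the bias if only completers are measured**

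In one arm, let p be the proportion stopping early, C the mean improvement of completers, S the mean improvement stoppers would have shown at the same time, and d = C − S.

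- Mean of all randomised = (1 − p)C + pS.
- Completer mean minus that mean = p(C − S) = pd.
- Bias in the A minus B difference = pA·dA − pB·dB.

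This is zero when both p and d are equal in the two arms. Equal stopping rates alone are not enough: with pA = pB = p the bias is p(dA − dB). When stoppers do worse, it favours the arm that more patients abandon. The direction reverses when patients stop because they have recovered.

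The protocol supplies none of these quantities. Purely as an illustration with a common d, assumed stopping rates of 20% and 5% and an assumed gap of 2 cm on the VAS give (0.20 − 0.05) × 2 = 0.30 cm. Rate differences of 0 to 15 points with gaps of 1 to 3 cm give 0 to 0.15 × 3 = 0.45 cm, in either direction. If d differs by arm, these values do not bound the bias.

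**The case against.** The strongest reply is that the protocol intends to assess everyone. Basic assumptions supposes that all patients attend the assessments, Data collection speaks of pain scores for all participants, and nothing restricts assessment to completers. With weekly sessions the visit also has a nominal time of about week 5 to 6. Windows and missing assessments are commonly left to an analysis plan, which is not shown here.

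Much of this stands. It rules out several stronger readings that a reader might infer:

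- **That early stoppers have no outcome visit at all.** The week-12 assessment does not depend on sessions received, and a patient who stops after session 3 or later can have the three-session assessment.
- **That the protocol prescribes different measurement times.** It prescribes weekly sessions for groups A and B. Times differ only if sessions are missed or delayed.
- **That the week-12 visit could precede the post-treatment visit.** Six weekly sessions would have to take about twice as long as planned, and nothing in the protocol suggests this.
- **That the two-month wording shows drift between patients.** It is a contradiction in the schedule that affects the planned calendar for everyone.
- **That a particular amount of bias can be stated.** Every input is assumed.

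What does not stand is that the intent settles the matter. An assumption of full treatment and attendance is not a procedure for the patient who breaks it, and the only trigger given cannot be met by that patient. When, and in whom, the outcome is collected belongs in the protocol. The week-12 visit is only a partial substitute: it is described as additional, has no stated starting point and is missing from one of the two visit descriptions.

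**Conclusion.** The point holds in this form. The post-treatment VAS and FFI are triggered by an event after randomisation, with no time anchor, no window and no provision for patients who stop treatment but remain in the study. For them the post-treatment measurement is undefined, and for patients who miss weeks it may be late. The between-group comparison at that visit could become one of completers.

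The size of any bias cannot be derived from the protocol. It is zero if stopping is equally frequent and alike across arms, and its direction depends on why patients stop. That this visit carries the main comparison is inferred from the Purpose of the study and the Control group - C text, since no primary time point is named. This is an inexpensive improvement that should be made; it does not invalidate the design.

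**What to change.** - Define the interim, post-treatment and week-12 assessments by time from randomisation, each with a stated window. Set the post-treatment date from the planned treatment calendar once the sponsor has reconciled the weekly schedule for groups A and B with the two-month wording under Extracorporeal shockwave therapy. Which calendar applies is for the sponsor to decide.
- List the same visits under Control group - C and Data collection.
- Hold every assessment for every randomised patient, whatever number of sessions was received.
- State that stopping treatment is not withdrawal from the study, so that the rule on destroying data is not applied to these patients.
- Record the date of each session received.
- For patients who do not attend, collect both outcomes remotely: the VAS, for example, on a mailed paper form, and the FFI by the same route or by telephone.

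The cost is protocol wording and a few extra contacts. Some patients will have had fewer than six sessions when measured, which is the price of comparing the groups as randomised.
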